### Inclusion and exclusion criteria

Eligible pregnant women will be enrolled via maternity healthcare centres in south-eastern Sweden. Inclusion criteria are as follows: confirmed diagnosis of GDM detected by an oral glucose tolerance test in accordance to local guidelines based on the WHO diagnostic criteria from 2013,^4 45^ and ability to read and speak Swedish, English, Arabic or Somali sufficiently well to be able to provide informed consent. Also, key intervention content is also summarised in audio-files, to facilitate for women with limited reading skills. Exclusion criteria include known pre-pregnancy diabetes, twin pregnancy, age below 18, severe comorbidities that would limit participation or a previously diagnosed severe psychiatric illness.

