#### Models

For the primary outcome TIR, we will use beta regression and report on the estimated OR with respect to group allocation. We will use linear regression for all other outcomes apart from the introduction of metformin/insulin treatment, adverse obstetric and neonatal outcomes, and adherence to the measurement protocol for daily glucose. The introduction of metformin/insulin treatment will be modelled using ordinal regression (no treatment<metformin<insulin), adverse outcomes will be modelled using negative binomial regression (counting the number of incidences adverse outcomes), and average measurement protocol adherence will be estimated using beta regression. Models will be adjusted for gestational week at baseline, age, pre-pregnancy Body Mass Index (BMI) (underweight and normal weight vs overweight and obese), previous GDM diagnosis, baseline HbA1c, as well as baseline measures of each respective outcome where available. For models of gestational weight gain, we will, in accordance with our previous trials,^22^ fit follow-up weight in gestational weeks 37–38 on group allocation and adjust for baseline weight as it is more robust against regression toward the mean. When relevant we will also additionally adjust for educational attainment (university degree vs no university degree).

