#### Ancillary analyses

We will study effect modification of the intervention on primary and secondary outcomes with respect to baseline variables. This will be done by estimating regression models with interaction terms between group allocation and baseline variables (one model per variable and outcome). The baseline variables of interest are the following: pre-pregnancy BMI (underweight and normal weight vs overweight and obese), parity (0 vs ≥1), educational attainment (university degree vs no university degree) and country of birth (foreign-born vs Swedish-born).

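### Pre-pregnancy BMI is cut into two groups in the outcome models' adjustment set and in the BMI interaction models; this loses a modest amount of precision and hides any gradient between overweight and obese women

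*Protocol article*

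**What the plan says.** In the protocol article, the Models section sets one covariate list for the outcome models. It opens "Models will be adjusted for gestational week at baseline, age, pre-pregnancy Body Mass Index (BMI" and codes BMI in two groups: "pre-pregnancy Body Mass Index (BMI) (underweight and normal weight vs overweight and obese". The rest of the list is "previous GDM diagnosis, baseline HbA1c, as well as baseline measures of each respective outcome where available". Education, also binary, may be added: "When relevant we will also additionally adjust for educational attainment (university degree vs no university degree". The weight-gain model has its own rule and will "fit follow-up weight in gestational weeks 37–38 on group allocation and adjust for baseline weight".

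Ancillary analyses fits one interaction model per baseline variable and outcome, with BMI cut at the same place: "pre-pregnancy BMI (underweight and normal weight vs overweight and obese), parity (0 vs ≥1".

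The article therefore fixes the coding and does not leave it to a later document. Neither section gives a reason for the split.

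**The concern.** BMI is continuous. A two-group term gives overweight women and women with any grade of obesity the same predicted outcome, and pools underweight with normal weight. Variation within each group that predicts the outcome goes into the residual, so the treatment effect is estimated less precisely than the collected data allow.

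Precision matters here for a reason beyond power. Under Statistical analyses, the trial reports 95% compatibility intervals and also the symmetric range around the null that holds 95% of the posterior, which is meant to inform implementation decisions. Both depend directly on posterior width.

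The second consequence concerns effect modification. A two-level BMI interaction yields one contrast, lower group against upper group. If the effect of SPARK differs between overweight and obese women, that model cannot show it.

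**Working it through.** **Figures from the plan (Sample size section).** TIR difference 5 points, SD 12, power 0.8, significance level 0.05, 360 completers. The article gives no figure for the prognostic value of BMI, so there is none to reproduce. For context:

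- Two-sample formula: n per arm = 2 × (12/5)² × (1.96 + 0.8416)² = 90.4, so 91 per arm and 182 in total. The 360 is not the minimum from this formula.
- With 180 per arm, SE = 12 × √(2/180) = 1.265 and power = Φ(5/1.265 − 1.96) = 0.977. The statement that 360 is enough is therefore true.

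The BMI point does not depend on how 360 was chosen.

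**Step 1: information kept by the split.** For a normal covariate with a linear effect, split so that a fraction p lies in the lower group, the share of explained variance kept is k = φ(z_p)² / [p(1 − p)].

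- 50/50: k = 2/π = 0.637
- 30/70: k = 0.576
- 16/84 (cut one SD below the mean): k = 0.439

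The splits are assumptions.

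**Step 2: effective sample size.** If BMI has correlation r with the outcome, the residual variance is proportional to 1 − r² with continuous BMI and to 1 − k r² with the split. The ratio (1 − k r²)/(1 − r²) is the gain from continuous BMI. The range r = 0.2 to 0.4 is assumed.

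| Lower/upper group | k | Ratio, r = 0.2 | Ratio, r = 0.4 |
|---|---|---|---|
| 50/50 | 0.637 | 1.015 | 1.069 |
| 30/70 | 0.576 | 1.018 | 1.081 |
| 16/84 | 0.439 | 1.023 | 1.107 |

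For example, 50/50 with r = 0.2 gives (1 − 0.637 × 0.04)/(1 − 0.04) = 0.9745/0.96 = 1.015.

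**Step 3: what this means for the intervals.** Interval width scales with the square root of the ratio: √1.015 = 1.008 and √1.107 = 1.052. Intervals are between just under 1% and about 5% wider. On the TIR scale with SD 12 and 180 per arm, the 95% half-width changes as follows:

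- r = 0.2, 50/50: 1.96 × 12 × √0.9745 × √(2/180) = 2.45 points with the split, against 2.43 with continuous BMI.
- r = 0.4, 16/84: 2.39 against 2.27 points.

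The difference is about 0.02 to 0.12 percentage points.

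**Step 4: power for the 5-point difference.** With BMI explaining 2% to 15% of the variance, power is 0.979 to 0.990 with continuous BMI, 0.978 to 0.986 with a 50/50 split, and 0.978 to 0.985 with a 30/70 split.

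**Step 5: interaction.** A binary BMI term supplies one interaction coefficient. Overweight and obese women share a code, so no contrast between them exists in the model, whatever the sample size.

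**The case against.** The case for leaving the plan alone has real force.

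- **No bias.** BMI is a baseline variable and allocation is randomised 1:1, so coarse coding does not distort the group comparison. This stands.
- **Small cost.** The sample size was planned on an unadjusted SD of 12, so it relies on no covariate gain. The correlations are assumed, and what BMI adds beyond age, previous GDM, baseline HbA1c and the baseline outcome may be smaller. The 11% needs both r = 0.4 and an 84% upper group; at 50/50 the top is about 7%. The formula is for a linear model, whereas TIR is analysed by beta regression, so it is only approximate there. All of this stands.
- **The interaction analysis is ancillary and all four modifiers are binary.** Uniform reporting is a fair aim, but it can be met by displaying categories while modelling BMI continuously.

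Some stronger readings are tempting, and the article does not support them.

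- A reader might infer that every model is affected. Attrition analyses states no BMI coding, and the weight-gain model also includes baseline weight.
- A reader might infer that the plan wastes the diagnostic glucose values, since eligibility requires "confirmed diagnosis of GDM detected by an oral glucose tolerance test". The article does not say that these values are recorded for the trial, and nothing in it shows what they would add to HbA1c and previous GDM. Leaving them out is a choice of covariates and not an error.
- A reader might argue that baseline HbA1c is a poor covariate because the Introduction says that it can be falsely low. That remark concerns HbA1c as a measure of foetal glycaemic exposure. A downward shift does not by itself remove its value for adjustment.
- A reader might infer that no baseline TIR exists. The Models section provides for baseline measures where available, and the study outline figure is not shown.

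**Conclusion.** The point holds as a minor one. The article explicitly fixes a two-group coding of BMI, without a reason, in the outcome models' adjustment set and in the BMI effect-modification models. Under a roughly normal BMI with a linear effect, the split loses about 36% of the linear information at 50/50 and about 42% at 30/70. With an assumed BMI–outcome correlation of 0.2 to 0.4, that is worth about 1.5% to 11% of effective sample size, or intervals just under 1% to about 5% wider. The documents give neither the BMI distribution nor the correlation, so these are ranges and not estimates.

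The loss is one of precision. It does not undermine the randomised comparison or the adequacy of 360 completers for TIR. The inability to see a gradient between overweight and obese women follows from the coding itself and needs none of these assumptions.

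**What to change.** Enter pre-pregnancy BMI as a continuous term, linear or restricted cubic spline, in the outcome models and in the BMI interaction model. Choose the form before outcomes are analysed by group. Keep the two categories for descriptive tables and for displaying the fitted effects. Centre and scale BMI so that the stated Student's t prior has a clear meaning for its coefficient.

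The cost is a change of wording and one to three parameters for BMI, with matching interaction terms in the effect-modification model. No new measurement is needed as long as BMI itself, and not only its category, is recorded.

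Optionally, if the diagnostic glucose values are already recorded for the trial, they could be added as continuous covariates to the TIR and HbA1c models. This is a suggestion and not a correction.

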Digital technologies are becoming important resources for healthcare services. Mobile health (mHealth) refers to the use of mobile and wireless devices (mobile phones, tablets, wearable sensors etc) with advantages such as real-time monitoring and feedback, less burden on healthcare systems as well as cost-effectiveness.^19^ mHealth has been successfully integrated into interventions to promote healthy diets, physical activity and weight loss.^20 21^ We have previously shown that a smart phone intervention (HealthyMoms) successfully improved eating habits and lowered gestational weight gain in healthy women during pregnancy.^22^ Given the positive effect of the app, it has the potential to be adapted and expanded to reach other pregnant populations as well, including women diagnosed with GDM. Recently, trials of mHealth interventions targeting GDM patients have shown promising results regarding compliance and glycaemic control,^23^,^27^ and women as well as healthcare professionals have expressed the potential of such tools.^28 29^ However, some of them were conducted in countries with healthcare systems that are not comparable to Swedish GDM care.^23 24 27 30^ Thus, even though principles for GDM management are similar to other countries and follow international guidelines with glucose monitoring, dietary and physical activity advice with escalation into pharmaceutical treatment (metformin, insulin) when required,^4^ there are differences in how primary and secondary care are organised and executed, which motivates mHealth interventions that are adapted and evaluated in the Swedish healthcare system. Furthermore, some of the previous interventions were used in addition to usual care rather than substituting physical healthcare visits,^24^,^27^ while other trials investigated a remote glucose management intervention without additional lifestyle interventions.^23^ Also, economic evaluation of mHealth interventions is largely lacking.^31^ Indeed, in the Swedish healthcare context, a high-quality trial investigating a holistic, theory-guided mHealth intervention for women with GDM is lacking. Furthermore, previous research has used HbA1c (glycosylated haemoglobin) as an outcome for glycaemic control. However, HbA1c only reflects an average measure for the preceding 8–10 weeks and may be a suboptimal measure of foetal glycaemic exposure since it can be falsely low due to increased erythropoiesis during pregnancy.^32^ Finally, migration continues to increase worldwide and many countries such as Sweden are increasingly becoming more ethnically and culturally diverse. It is well-known that GDM is more prevalent among non-European populations,^33^ and recent reports also indicate that this applies to Sweden in both first and second generation immigrants.^34 35^ Adaptations and tailoring for foreign-born women who do not speak Swedish are thus essential to enable interventions to become accessible and inclusive for all women.^36^

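### Adjustment for education is left open in every main model, and parity, though available at baseline, is missing from the models of obstetric and neonatal outcomes that have no baseline value

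*Protocol article*

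**What the plan says.** The Models section opens the adjustment set with "Models will be adjusted for gestational week at baseline, age, pre-pregnancy Body Mass Index (BMI" (in two classes) and completes it with "previous GDM diagnosis, baseline HbA1c, as well as baseline measures of each respective outcome where available". It then adds one conditional covariate: "When relevant we will also additionally adjust for educational attainment (university degree vs no university degree". The sentence is not tied to any outcome, so it also reaches the primary analysis: "For the primary outcome TIR, we will use beta regression and report on the estimated OR with respect to group allocation".

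The Ancillary analyses section lists the effect modifiers. Besides BMI class they are "parity (0 vs ≥1), educational attainment (university degree vs no university degree) and country of birth (foreign-born vs Swedish-born". All are two-level baseline variables. BMI class is also in the fixed set, education is there conditionally, and parity and country of birth are not there.

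The section on adverse obstetric and neonatal outcomes lists items that arise in late pregnancy, at delivery or in the infant, such as pre-eclampsia, mode of delivery, infant hypoglycaemia and birth weight. Under Models, adverse outcomes are analysed as a count by negative binomial regression.

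**The concern.** There are two separate issues.

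**Education.** A conditional covariate with no stated condition leaves a modelling choice open on every outcome. The plan reports, for each outcome, a posterior probability of benefit and a symmetric range around the null, and says that the contrast bears on implementation decisions. Both quantities can move when education enters or leaves the model. In a logit-link beta regression the odds ratio is also conditional on the covariates, so the target of estimation moves as well as its precision.

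**Parity.** The rule of adjusting for the baseline measure of the outcome gives nothing for outcomes that do not exist at baseline. For those, precision from covariates can come only from the general list. Previous GDM does not replace parity. A yes implies an earlier pregnancy, but a no pools first-time mothers with parous women who had no earlier GDM.

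**Working it through.** The plan gives no figure on this point. The usable inputs, from the Sample size section, are 360 completers (taken as 180 per arm), SD 12 percentage points and a difference of 5 points. Everything marked *assumed* is not in the documents.

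**1. TIR: gain in precision.** The standard error (SE) of the unadjusted difference is 12 × √(2/180) = 1.265 points. By the two-sample formula (two-sided 5%), power is 0.977, above the plan's target of 0.8. If a further covariate explains a share R² of variance (*assumed*), the SE is multiplied by √(1 − R²):

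| Extra R² | SE reduction | Power |
|---|---|---|
| 1% | 0.5% | 0.978 |
| 5% | 2.5% | 0.982 |
| 10% | 5.1% | 0.986 |

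**2. TIR: how far the estimate can move.** The difference between the analyses with and without education has SD of about √R² × 1.265 points. That is 0.18 points at R² = 2% and 0.40 at R² = 10%, against a target of 5.

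The change in the odds ratio itself is smaller. For TIR of 70% against 75% it is (0.75/0.25)/(0.70/0.30) = 1.286. Split the control mean into two equal education groups at 70 ± 12√R² points and keep the overall means at 70% and 75%. The within-group odds ratio is then 1.286 at R² = 2% and 1.288 at R² = 10%.

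**3. Choosing between two education analyses.** With no true effect, the two test statistics are approximately standard normal with correlation √(1 − R²). The chance that the larger exceeds 1.96 is 2.8% at R² = 2% and 3.2% at R² = 10%, against a nominal 2.5%. A two-sided simulation (360 women, education split 50:50 *assumed*, 40,000 runs) took 5% to about 5.4%, 6.0% and 6.4% at R² of 1%, 5% and 10%.

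**4. Parity and the adverse-outcome count.** With nulliparous share p, parity rate ratio RR, mean count μ and residual dispersion k:

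- CV² = p(1 − p)(RR − 1)² / [1 + p(RR − 1)]²
- share of the variance of the log rate ratio ≈ CV² / (1/μ + k + CV²)

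With p = 0.45 (*assumed*), CV² is 0.0891/1.6129 = 0.0552 at RR 1.6 and 0.2475/2.1025 = 0.1177 at RR 2.0.

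| μ | RR | k = 0 | k = 0.5 |
|---|---|---|---|
| 0.7 | 1.6 | 3.7% | 2.8% |
| 0.7 | 2.0 | 7.6% | 5.8% |
| 1.5 | 1.6 | 7.7% | 4.5% |
| 1.5 | 2.0 | 15.0% | 9.2% |

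The range is about 3–15% of variance. At the top the SE falls by 1 − √0.85 = 7.8%. Overlap with previous GDM, already adjusted for, would lower every cell.

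**5. Parity and continuous outcomes such as birth weight.** R² = p(1 − p)d² = 0.2475d². An *assumed* parity difference d of 0.2–0.5 SD gives 1–6%.

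**The case against.** The strongest reply is that the covariate list is already prespecified and sensible, that one more covariate is a matter of preference, and that leaving out a baseline covariate does not bias a randomised comparison. All of that stands. So does the small gain on TIR, and so does the fact that the count calculation rests on assumptions. Treating the count as Poisson apart from parity would give only the upper column.

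Three stronger readings are tempting, and the documents support none of them.

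- *Known prognostic information is wasted.* The article nowhere says that parity or country of birth predicts any trial outcome among women with GDM. On origin it says only "It is well-known that GDM is more prevalent among non-European populations", which concerns prevalence. An effect modifier need not be an adjustment covariate, and these variables are used in the ancillary models.
- *The interaction models condition on a different covariate set.* The article describes them as "estimating regression models with interaction terms between group allocation and baseline variables (one model per variable and outcome" and does not state their other covariates. An interaction model would in any case normally include the modifier's main effect.
- *Two versions of each result will be produced and the better one reported.* Nothing says so. The error figures show what selective use would do. The Sample size section also says that null-hypothesis testing is not the basis for inference, so they are only a guide.

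It may also be said that a fuller analysis plan could define the condition for education. It could, but the article does more than stay silent: it states a rule whose condition is open. The Bayesian framework does not close it, since the posterior probability and the symmetric range depend on the model chosen.

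**Conclusion.** The point holds in two limited parts. Adjustment for education is left to discretion in all main models, the primary one included. Parity is available at baseline but left out where no baseline outcome can supply precision.

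The consequence for TIR is small: power moves from 0.977 to at most 0.986 at an assumed extra R² of 10%, and the estimate typically shifts by a few tenths of a point. For the adverse-outcome count the gain is modest, about 3–15% of variance under the assumptions shown and less after overlap with previous GDM. No figure in the documents supports a gain from country of birth. The validity of the randomised comparison is not in question. What is at issue is an avoidable choice and some precision available at no cost.

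**What to change.** In the Models section, delete the qualifier on education and place it in the fixed covariate set of every main model. Add parity (0 vs ≥1) to the fixed set, at least for the obstetric and neonatal outcomes. Country of birth may be added on the same basis but is not essential. Make the change before outcome data are seen, and report it in the trial registration, as the article promises for amendments.

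The cost is a sentence of text and one or two extra parameters with about 360 women. No new data are needed, since the plan already uses both variables as baseline effect modifiers.

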#### Ancillary analyses

We will study effect modification of the intervention on primary and secondary outcomes with respect to baseline variables. This will be done by estimating regression models with interaction terms between group allocation and baseline variables (one model per variable and outcome). The baseline variables of interest are the following: pre-pregnancy BMI (underweight and normal weight vs overweight and obese), parity (0 vs ≥1), educational attainment (university degree vs no university degree) and country of birth (foreign-born vs Swedish-born).

#### Attrition analyses

We will investigate if there is systematic attrition by estimating logistic regression models with response/no-response as outcome. These models will include baseline variables as covariates and interaction terms between baseline variables and group allocation. We will use shrinkage priors to account for the excessive number of parameters in these models.

### Sample size

We conducted a Monte Carlo study to estimate the number of participants we need to recruit. We simulated scenarios where the difference in TIR between groups at follow-up was five percentage points, which is of clinical relevance in diabetic women to lower the risk of adverse pregnancy outcomes.^66^ The differences between groups that we simulated started from 70% TIR in the control group and 75% in the intervention group to 90% TIR in the control group and 95% in the intervention group. We used an SD of 12 percentage points in both groups in all simulations. Aiming for a power of 0.8 at the 0.05 significance level, we found that with 360 women completing follow-up we will have enough power to detect a statistically significant effect in all the scenarios simulated. Based on our previous interventions,^22^ we expect a dropout rate of 10%–15% and will therefore recruit 412 participants. It should be noted that our analyses follow a Bayesian paradigm where null-hypothesis testing is not the basis for scientific inference; thus, a predetermined sample size to protect against type I and II errors is not required. Therefore, the function of our power calculation is only to give a target for recruitment.

